#### Blinding

2.3.2

This study adopts a single-blind design. Due to the nature of the interventions, participants and intervention providers cannot be blinded. However, research assistants responsible for collecting outcome data and statisticians conducting the final data analysis will remain blinded to group allocation. Research assistants will not know participants’ group assignments during clinical measurement and questionnaire collection. Statisticians will analyze de-identified datasets and will not access files containing allocation information before the analysis is completed.

### Interventions

2.4

All three groups will undergo a 3-month intervention period.

#### Control group (CG)

2.4.1

Participants will receive routine chronic disease management, including outpatient follow-up, health education, medication guidance, and monitoring of blood pressure, blood glucose, and blood lipids. They will not access the AI-HEALS platform, nor undergo TCM constitution assessment.

#### Universal AI-HEALS Group (UG)

2.4.2

In addition to routine chronic disease management, this group will receive an AI-HEALS-based intelligent health education intervention delivered through a WeChat Mini Program. The intervention operates via three core modules: rule base construction, article recommendation, and an intelligent Q&A system. The platform implements a combined model of “menu-driven self-intervention and targeted content delivery “to provide continuous, individualized, and adaptive health education and behavior support for patients with hypertension, hyperlipidemia, and diabetes multimorbidity”. The platform also includes the following ancillary and adherence-support features: Daily reminders: The system automatically sends daily tips on diet, exercise, and daily routines. A check-in function allows participants to log completion of recommended behaviors and record blood pressure and glucose measurements; Additional support: Research staff will provide telephone assistance to each participant to ensure smooth operation of the platform throughout the intervention period. High-adherence criterion: Participants will be classified as highly adherent if they log into the system on at least 3 days per week during the intervention phase.

#### TCM-Adapted AI-HEALS Group (TG)

2.4.3

This group receives routine care and uses AI-HEALS enhanced with a TCM-expert-curated knowledge base to deliver constitution-based personalized interventions.

Platform initialization and constitution profiling: During the first use of -AI-HEALS, participants will complete TCM constitution identification using the relevant scale, along with baseline self-report questionnaires and entry of key health indicators (e.g., blood pressure, blood glucose, lipid profiles)Personalized health profiling: Based on the 30-item simplified Constitution in Chinese Medicine Questionnaire (CCMQ-30) (37), the system automatically identifies the participant’s constitution type. By integrating disease status, lifestyle habits, and symptomatic manifestations, it generates a personalized “health profile” to inform subsequent tailored interventions.Interactive support: Users can actively ask questions through text or voice input and receive individualized health consultation and management advice. The platform homepage also provides structured menu access, allowing participants to browse health topics of interest.

All intervention content is designed according to TCM constitution and covers core domains: dietary adjustment, exercise guidance, daily routine regulation, emotional regulation, and related health-preservation advice.

Introduction to TCM constitution is provided in Appendix 1 in Supplementary Material.

TCM-based health education materials are provided in Supplementary material 1.

### Outcomes

2.5

Data will be collected at baseline (T0), month 3 (T1), and month 6 (T2).

#### Primary outcome

2.5.1

Change in systolic blood pressure from baseline to month 3 (T1). Systolic blood pressure (SBP) is selected due to its continuous, independent, and direct positive association with cardiovascular risk (2), and strong evidence that effective SBP control reduces cardiovascular events and all-cause mortality (38).

#### Key secondary outcomes

2.5.2

Physiological indicators: HbA1c, blood fat, BMI, diastolic pressure.Self-management behavior modification: ability to self-manage chronic disease, medication adherence, physical activity, level of engagement, Self-Regulation of Eating Behavior.Quality of life and psychological indicators: quality of life, anxiety, depression, self-efficacy, Perceived Social Support.

#### Exploratory outcomes

2.5.3

TCM constitution indicators: constitution type transformation.

Timing of measurements is shown in Table 1.

**Table 1 tab1:** Schedule of evaluations.

Study period	Recruitment	Intervention	Follow-up
Informed consent	√		
Demographics	√		
Physiological indicators	√	√	√
Medical history and medication use	√	√	√
CCMQ-30	√	√	√
CDSMS	√	√	√
PHQ-4	√	√	√
EQ-5D-5L	√	√	√
ARMS-7	√	√	√
NGSES	√	√	√
PSSS	√	√	√
SREBQ	√	√	√

CCMQ-30, Constitution in Chinese Medicine Questionnaire–30-Item Short Form; CDSMS, Chronic Disease Self-Management scale; PHQ-4, the abbreviated Patient Health Questionnaire-4; EQ-5D-5L, EuroQol-5 Dimensions 5 Levels; ARMS-7, Adherence to Refills and Medications Scale-7; NGSES, New General Self-Efficacy Scale; PSSS, The Perceived Social Support Scale; SREBQ, The Self-Regulation of Eating Behavior Questionnaire.

### Collected information

2.6

We will collect sociodemographic information, including: age, sex, marital status, type of medical insurance, education level, employment status, household income, smoking history, drinking history, etc.

#### Blood pressure measurement

2.6.1

Blood pressure will be measured using hospital-certified and fully calibrated electronic devices. During measurement, participants will sit quietly for at least 5 min, relax their body, maintain the upper arm at heart level, and remain seated. After 30–60 s, the measurement will be repeated, and the average of two readings will be used.

#### BMI measurement

2.6.2

These will be measured twice using hospital-certified and fully calibrated instruments. BMI will be calculated as weight (kg) divided by height (m).

#### Process indicators

2.6.4

System usage frequency, function usage preferences, and intervention satisfaction assessed through interviews.

### Statistical analysis

2.7

Statistical analyses will be performed using SPSS 26.0 (or R). Continuous variables with normal distribution will be presented as mean ± standard deviation; non-normally distributed variables as median (interquartile range).

All primary and key secondary analyses will adhere to the intention-to-treat principle. To evaluate the effect of the intervention on health outcomes, under the assumption of data missing at random, a linear mixed-effects model will be applied. Time, group, and their interaction will be included as fixed effects, and a random intercept will be added for each participant to control for baseline heterogeneity. Baseline values and age will be included as covariates.

Between-group differences at each time point will be estimated using the EMMEANS package to compute estimated marginal means (EMMs), followed by adjusted pairwise comparisons (e.g., Tukey multiple comparison tests). To assess overall changes from baseline to the end of follow-up, model-estimated baseline-adjusted marginal means at the endpoint will be compared among the three groups. The family-wise error rate for primary and key secondary outcomes will be controlled using the Bonferroni method. A *p*-value < 0.05 will be considered statistically significant.

Sensitivity analyses will be conducted to assess the robustness of the findings:

Adherence analyses: To examine the impact of intervention adherence, a per-protocol analysis will be performed. Participants meeting the pre-defined criterion for high adherence will be included, and results will be compared with the primary intention-to-treat analysis.Missing Date: To evaluate the robustness of findings against departures from the missing-at-random assumption, a worst-case scenario analysis will be performed. In this analysis, missing values in the intervention groups will be imputed under the assumption of clinical deterioration, whereas missing values in the control group will be imputed under the assumption of improvement.Exploratory analyses will be conducted to generate hypotheses for future research. These will include:Subgroup analyses: Treatment effect heterogeneity will be explored across subgroups defined by baseline characteristics (e.g., age, sex, having all three conditions) by adding relevant interaction terms to the linear mixed-effects model.Analysis by Comorbidity Pattern: This analysis will specifically examine whether intervention effects differ among participants with varying multimorbidity patterns (e.g., hypertension + diabetes vs. Hypertension +hyperlipidemia vs. all three conditions).

Results from all Exploratory Analysis will be interpreted with caution due to reduced statistical power. For exploratory outcomes (TCM constitution type transformation), the focus will be on estimating effect sizes and confidence intervals rather than hypothesis testing. When multiple *p*-values need to be combined, Stouffer’s Z-score method will be utilized.

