### Study design

2.1

This study will adopt a single-blind, three-arm parallel randomized controlled trial design. Participants will be recruited from a Class A secondary hospital in Zhejiang Province, China. All enrolled patients will receive standard chronic disease management in accordance with *Expert consensus on standardized diagnosis and treatment of coexisting hypertension, hyperglycemia, and hyperlipidemia in China (2023 edition)* (3). The intervention period will last for 3 months, followed by continued observation until month six to assess the sustainability of short-term effects. The three groups differ in the additional interventions provided:

Control Group (CG): Routine chronic disease management only.Universal AI-HEALS Group (UG): Routine management plus access to the AI-HEALS WeChat Mini Program (universal version).TCM-Adapted AI-HEALS Group (TG): Routine management plus access to the AI-HEALS WeChat Mini Program (TCM-adapted version).

The study flow and group allocation are shown in Figure 1.

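### As described, the mixed model assumes one residual variance and one baseline slope for months 3 and 6; if the visits differ, the visit-specific standard errors are biased, in a direction the protocol cannot settle

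*Protocol article*

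**What the plan says.** Section 2.7 applies one linear mixed model to the health outcomes. On the fixed part it says: "Time, group, and their interaction will be included as fixed effects". On the within-participant part and the covariates it says: "a random intercept will be added for each participant to control for baseline heterogeneity. Baseline values and age will be included as covariates". It names no random slope, no visit-specific residual variance and no baseline-by-time term. It does not say whether T0 is a response row as well as a covariate.

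The contrasts come from this same model: "Between-group differences at each time point will be estimated using the EMMEANS package". The primary outcome (2.5.1) is the change in systolic blood pressure from baseline to month 3. Month 6 has its own purpose in Study design (2.1), where the 3-month intervention is "followed by continued observation until month six to assess the sustainability of short-term effects".

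The only variability figure is a single SD of 16.3 mmHg common to the groups (2.2.1). The protocol gives no SD by visit, no month-6 SD and no correlation between visits.

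**The concern.** A participant random intercept with homogeneous residuals is a compound-symmetry model. It estimates one total residual variance and uses it for the contrast at every visit. A baseline main effect without a time interaction also fits one slope to both visits.

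The visits differ by design: T1 falls at the end of the intervention and T2 three months after it stops. Equal variance and an equal baseline slope are therefore assumptions, and the protocol offers no figure in their favour. If they fail, the averaged variance is too large for one visit and too small for the other. One visit then loses power and the other rejects too often. The month-3 contrast is the primary one, and the month-6 contrast carries the claim of sustained effect.

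**Working it through.** **The plan's own figure.** The means 138.2, 132.0 and 127.0 average 132.4. The squared deviations are 33.64, 0.16 and 29.16, so the SD of the means is √(62.96/3) = 4.58 and f = 4.58/16.3 = 0.281. One-way ANOVA at α = 0.05 gives power 0.898 at 54 per group and 0.903 at 55. Then 165/0.8 = 206.25, which rounds up to 207, or 69 per group. The sample size reproduces and does not depend on this point.

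**Inputs.** From the protocol: 55 per group, SD 16.3 mmHg, the means above. Assumed, because the protocol gives none: correlations r₃ (T0 with T1) and r₆ (T0 with T2), and any SDs that differ by visit. Data are complete, and T0 is a covariate only unless stated.

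**Formulas, equal SDs, variances in units of 16.3².**
- Common slope: b = (r₃ + r₆)/2.
- Residual variance at a visit: v = 1 − 2b·r + b².
- Variance the model uses at both visits: the average of v₃ and v₆.
- SE of a pairwise contrast: √(2 × 16.3² × v/55) = √(9.66·v).
- Approximate two-sided test size: P(|Z| > 1.96 × model SE/actual SE).

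**Example, r = 0.6/0.5.** b = 0.55; v₃ = 1 − 0.66 + 0.3025 = 0.6425; v₆ = 1 − 0.55 + 0.3025 = 0.7525; average 0.6975. The ratio of model to actual SE is √(0.6975/0.6425) = 1.04 at month 3 and √(0.6975/0.7525) = 0.96 at month 6.

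**Example, r = 0.7/0.5.** b = 0.6; v₃ = 0.52; v₆ = 0.76; average 0.64. The ratios are √(0.64/0.52) = 1.11 and √(0.64/0.76) = 0.92.

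**Example, SDs 18/15, r = 0.5/0.5, baseline SD 16.3.** The visit slopes are 0.552 and 0.460, common slope 0.506. The residual variances are 324 × 0.75 + 0.046² × 265.69 = 243.6 and 225 × 0.75 + 0.046² × 265.69 = 169.3, average 206.4. The ratios are √(206.4/243.6) = 0.92 and √(206.4/169.3) = 1.10.

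| Assumed r (T0–T1 / T0–T2) | Assumed SDs, months 3/6 | Actual SE, months 3/6 | Model SE | Ratio, months 3/6 | Approx. test size, months 3/6 |
|---|---|---|---|---|---|
| 0.5/0.5 | 16.3/16.3 | 2.69/2.69 | 2.69 | 1.00/1.00 | 5.0%/5.0% |
| 0.6/0.5 | 16.3/16.3 | 2.49/2.70 | 2.60 | 1.04/0.96 | 4.1%/5.9% |
| 0.6/0.4 | 16.3/16.3 | 2.51/2.87 | 2.69 | 1.07/0.94 | 3.5%/6.6% |
| 0.7/0.5 | 16.3/16.3 | 2.24/2.71 | 2.49 | 1.11/0.92 | 3.0%/7.2% |
| 0.6/0.5 | 15/18 | 2.29/2.97 | 2.65 | 1.16/0.89 | 2.3%/8.0% |
| 0.5/0.5 | 18/15 | 2.98/2.48 | 2.74 | 0.92/1.10 | 7.1%/3.0% |

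**Simulation.** With T1–T2 correlation 0.6 and 20,000 null trials per set, the test size for r = 0.6/0.5, 0.6/0.4 and 0.7/0.5 was 4.0%, 3.5% and 3.1% at month 3, and 5.7%, 6.8% and 6.9% at month 6. This agrees with the closed form.

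**Power at month 3 in those same three sets.** With the plan's means, Tukey adjustment and 8,000 trials per set, freeing both variance and slope raised power as follows:
- Universal versus control (difference 6.2): 51% to 55%, 47% to 54%, 56% to 67%.
- TCM-adapted versus universal (difference 5.0): 33% to 36%, 30% to 36%, 35% to 45%.

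Most of the gain comes from the variance. At r = 0.7/0.5, a visit-specific slope only lowers the actual month-3 SE from 2.24 to √(9.66 × 0.51) = 2.22.

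**If T0 is also a response row.** Take r = 0.5/0.5 and equal SDs: b = (1 + 0.5 + 0.5)/3 = 0.667. The residual variances are 0.111 at T0 and 0.778 at each later visit, average 0.556. The ratio is √(0.556/0.778) = 0.85 at both visits, a test size of about 9.8%. Over the five sets tried under this reading (the table's, without 0.7/0.5), the month-3 ratio ran from 0.79 to 0.97 and the month-3 test size from 5.7% to 12.4%.

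**The case against.** The strongest reply has three parts.

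1. **The text does not compel equal variances.** A random intercept can be combined with visit-specific residual variances. The residual structure is a detail that an article often leaves to a fuller plan, which is not shown. This stands in part. It would be wrong to say the protocol forces equal variances. But the section does name a structure and a covariate list, and their plain reading with default residuals is the restrictive model.

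2. **The direction is unknown.** A reader might infer that month-3 intervals are definitely too wide and month-6 intervals too narrow, because baseline usually predicts a nearer visit better. The protocol does not support that. It gives one SD and no correlations. Equal values give no distortion, SDs of 18/15 reverse it, and T0 as a response row makes month-3 intervals too narrow in every case tried. This objection stands, so the direction can only be stated conditionally.

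3. **The effect is modest and the model conventional.** Where baseline predicts month 3 better, the primary test is conservative, and the inflation falls on month 6, which is not primary. In the mildest distorting case, the power gain is 3 to 4 points. This is fair and limits the weight of the point. It does not argue for keeping an assumption that costs almost nothing to drop.

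**Conclusion.** The point holds in conditional form. On its plain reading, the model in 2.7 assumes the same residual variance and the same baseline slope at months 3 and 6, and no figure in the protocol supports that.

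The consequence depends on quantities the protocol does not give. It ranges from nothing, through lost power on the primary contrast with month-6 tests at roughly 6% to 7% (the three equal-SD sets with unequal correlations), to a primary test at about 7% if month-3 variance is the larger. All of these rest on assumed correlations and SDs, complete data at 55 per group, and T0 as covariate only. The protocol cannot say which case applies. That is a reason to free the structure, not evidence that the planned result will be wrong.

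This is a free improvement rather than an error that must be corrected.

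**What to change.** In section 2.7:
- State that T1 and T2 are the only response rows and that T0 enters as a covariate.
- Replace the participant random intercept with an unstructured within-participant covariance over T1 and T2.
- Add a baseline-by-time interaction to the fixed effects.
- Take the month-3 primary contrasts and the month-6 contrasts from that model.

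With two post-baseline visits, this adds one covariance parameter (three instead of two) and one slope. It needs no new data, visits or participants. It remains valid whether or not the two visits differ, and it also removes the doubt about T0 as a response row. It can be settled in a sentence or two before unblinding.

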To evaluate the effectiveness of the AI-HEALS system—particularly its TCM-adapted version—compared with routine management and generalized mobile health interventions in improving clinical outcomes among patients with chronic disease multimorbidity.To assess the effectiveness of the system in enhancing chronic-disease self-management behaviors.

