#### Recruitment and sample size

2.2.1

This study plans to use a consecutive enrollment strategy between February 2026 and December 2026. Specialized personnel from the hospital Information Department (not involved in this study) will conduct an initial screening of anonymized data from the electronic health record system to identify patients who meet the diagnostic criteria for multimorbidity. Subsequently, research assistants will independently review the data in pairs based on predetermined inclusion and exclusion criteria. Once eligibility is confirmed, independent recruitment staff will contact potential participants using compliant contact information recorded in the hospital system and invite them to join the study after obtaining informed consent.

The sample size calculation is based on the primary outcome (systolic blood pressure). According to previous similar research (34–36), the optimistic but clinically significant effect size hypothesis was adopted. The expected systolic blood pressure after 3 months of intervention is set as follows: 138.2 mmHg for the routine health education group, 132.0 mmHg for the universal AI group, and 127.0 mmHg for the TCM-constitution–based AI group. The common inter-group standard deviation (*σ*) is set at 16.3 mmHg. Using G*Power 3.1 software with one-way ANOVA (F tests), two-sided *α* = 0.05, and power (1 − *β*) = 90%, the required sample size is 55 participants per group, totaling 165 participants. Considering an estimated 20% dropout rate, the final planned recruitment is 207 participants, or 69 per group. If the true intervention effect size is smaller than the assumed, the statistical power of this study will be correspondingly reduced, and the results should be interpreted with caution and regarded as preliminary exploratory evidence.

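### With exactly three arms, a closed test (2-df month-3 contrast, then unadjusted pairs) holds the same 5% family-wise error as Tukey, the only pairwise method named, with more power on TG-UG and UG-CG

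*Protocol article*

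**What the plan says.** Section 2.7 (Statistical analysis) fits a linear mixed model with time, group and their interaction, and takes estimated marginal means at each time point, "followed by adjusted pairwise comparisons (e.g., Tukey multiple comparison tests"). It adds a Bonferroni correction across the primary and key secondary outcomes without giving the size of that family. It states no omnibus gate or closed procedure for the pairwise contrasts.

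Section 2.2.1 (Recruitment and sample size) sizes the trial on a different test: "Using G*Power 3.1 software with one-way ANOVA (F tests"), with "two-sided *α* = 0.05" and 90% power, giving 55 per group. The assumed month-3 values are "138.2 mmHg for the routine health education group", "132.0 mmHg for the universal AI group" and "127.0 mmHg for the TCM-constitution–based AI group"; the common standard deviation "is set at 16.3 mmHg".

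The aims in section 1 need more than one contrast: the system, and its TCM-adapted version in particular, is to be "compared with routine management and generalized mobile health interventions in improving clinical outcomes".

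**The concern.** TG-UG is the only contrast that isolates the TCM content, and UG-CG is the one that isolates the app. Both have small assumed differences (5.0 and 6.2 mmHg), so the pairwise cutoff matters most for them.

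Tukey is a single-step method. Its critical value is set for the case in which all three means are equal, and it applies that value to every pair whatever the other comparisons show. With three arms this is stricter than necessary. If any two of the three pairwise null hypotheses are true, all three means are equal, so the only intersection hypothesis is the global one. Once that has been rejected at 5%, each pair can be tested at 5% with strong family-wise control. What the plan could gain at no cost in patients is power on the two contrasts where it is weakest.

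**Working it through.** **Inputs** (section 2.2.1): means CG 138.2, UG 132.0 and TG 127.0 mmHg; SD 16.3; alpha 0.05; 55 evaluable and 69 recruited per arm. The differences are UG-CG 6.2, TG-UG 5.0 and TG-CG 11.2.

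**1. The plan's own figure.** Grand mean = 397.2/3 = 132.4. Deviations are 5.8, -0.4 and -5.4, with squares summing to 33.64 + 0.16 + 29.16 = 62.96. SD of the means = sqrt(62.96/3) = 4.581, so f = 4.581/16.3 = 0.281. With N = 165, lambda = 165 × 0.281² = 13.03 (unrounded f). The noncentral F with 2 and 162 df gives power 89.8% at 54 per arm and 90.3% at 55. The stated 55 reproduces, and 55/0.8 rounds up to 69. The sample-size arithmetic is not in question.

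**2. Cutoffs at 55 per arm.** SE of a pairwise difference = 16.3 × sqrt(2/55) = 3.11 mmHg.
- Tukey: studentized range (0.95; 3, 162)/sqrt(2) = 2.365, so an observed difference of about 2.365 × 3.11 = 7.4 mmHg is needed.
- Unadjusted t on 162 df: 1.975, so about 1.975 × 3.11 = 6.1 mmHg is needed, given a significant omnibus test.

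**3. Power.** 1,000,000 simulated trials with pooled variance; the closed test rejects a pair when F is significant at 5% and |t| exceeds the unadjusted cutoff.

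| Contrast | Tukey, n = 55 | Closed, n = 55 | Tukey, n = 69 | Closed, n = 69 |
|---|---|---|---|---|
| TG-UG | 22.8% | 35.7% | 29.0% | 43.3% |
| UG-CG | 35.8% | 50.3% | 45.1% | 60.1% |
| TG-CG | 89.1% | 90.0% | 95.2% | 95.6% |

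At 55 per arm the gains are 12.9, 14.5 and 0.9 points. The chance of at least one rejection is about 90% under both rules; the chance of rejecting all three pairs goes from 3% to 11%. To match the closed test's power at 55, Tukey would need about 84 per arm for TG-UG and about 77 for UG-CG.

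**4. Family-wise error at 55 per arm.** All means equal: 5.0% for both. Two means equal and the third 6.2, 11.2 or 100 mmHg away: about 1.9% for Tukey, 4.5% to 5.0% for the closed test.

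**5. Sensitivity to baseline adjustment.** The document gives no baseline to month-3 correlation. Assumed values of 0.3 to 0.7 scale the SD by sqrt(1 - rho²). At 0.5, TG-UG goes from 31% to 45% and UG-CG from 48% to 63%. Across the range the gain stays at about 13 to 15 points on both contrasts.

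**6. Sensitivity to the outcome-level Bonferroni.** If it also reduces the primary alpha (assumed family sizes, n = 55):

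| Alpha | TG-UG, Tukey to closed | UG-CG, Tukey to closed |
|---|---|---|
| 0.05/2 | 15.6% to 25.6% (+10) | 26.6% to 39.2% (+13) |
| 0.05/5 | 9.2% to 16.0% (+7) | 17.4% to 27.0% (+10) |
| 0.05/15 | 4.8% to 8.7% (+4) | 10.0% to 16.3% (+6) |

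**The case against.** The strongest reply is that nothing here is wrong. Tukey is standard for all-pairs comparisons, controls family-wise error at 5%, is named only as an example, and the final choice may sit in an analysis plan that is not shown. It also gives simultaneous intervals that agree with its tests and needs no gate, which suits a trial presented as preliminary evidence. All of this stands, and it is why the point is an improvement and not a fault. It does not remove the case for naming the closed rule now: the current wording admits it, but it could not credibly be adopted once results are known.

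The price is real but small. An unadjusted interval can exclude zero when the gate fails. At the plan's inputs and 55 per arm this occurs in about 94.8% - 90.0% = 4.8% of trials for TG-CG and in under 1% for each of the other two contrasts. In about 0.7% of trials Tukey would declare a pair different although the omnibus test is not significant.

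Three stronger readings are tempting, and the documents do not support them:
- That Tukey guards against configurations that cannot occur with three arms. Its cutoff is set for all means equal, which can occur; it is conservative because it is single-step.
- That the omnibus test used for sizing has been dropped. The mixed model contains group and group-by-time terms, and section 2.7 has the endpoint means compared among the three groups. What is absent is an omnibus gate.
- That the gain is 13 to 15 points regardless. That holds only if the primary outcome keeps alpha 0.05.

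**Conclusion.** The point holds as a cheap improvement. With exactly three arms, the closed test keeps the 5% family-wise error that Tukey provides and, at the plan's own inputs with 55 per arm and alpha 0.05, adds about 13 points of power on TG-UG and 14 to 15 on UG-CG. It leaves TG-CG and the chance of any finding essentially as they are.

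This rests on the section 2.2.1 means and SD, equal evaluable arms, and one outcome at one time point. How much survives the Bonferroni step depends on a family size that the document does not state. Even at full alpha, TG-UG reaches only about 36% and UG-CG about 50%, so the change does not replace stating pairwise power for these contrasts. The argument would not carry over to a fourth arm.

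**What to change.** In section 2.7, before any comparative data are seen, replace the parenthesis that names Tukey with:

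> *At month 3 the 2-df group contrast from the mixed model is tested first, at the level assigned to the outcome. Only if it is significant are TG-UG, TG-CG and UG-CG each tested at that same level without further adjustment (closed testing, three arms).*

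Report unadjusted 95% intervals labelled as not simultaneous, with Tukey simultaneous intervals alongside if wanted.

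The cost is this wording; no patients or data are involved. In exchange, no pairwise claim can be made when the omnibus contrast is not significant, and intervals and tests may occasionally disagree.

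### The single Bonferroni family over the primary and all key secondary outcomes puts the SBP test at about 0.0033, but the sample size assumes 0.05, so the stated 90% power does not hold under the plan's own rule

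*Protocol article*

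**What the plan says.** Three parts of the protocol article bear on this point.

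- **Statistical analysis (2.7).** The multiplicity rule is "The family-wise error rate for primary and key secondary outcomes will be controlled using the Bonferroni method". The next sentence gives the threshold: "p*-value < 0.05 will be considered statistically significant". It does not say whether this means a raw or an adjusted p-value. Pairwise group comparisons are handled just before, by an adjusted procedure with Tukey as the example.
- **Outcomes (2.5).** There is one primary outcome, the change in SBP from baseline to month 3. The section on key secondary outcomes lists 14 items: four physiological (HbA1c, blood fat, BMI, diastolic pressure), five behavioural ("ability to self-manage chronic disease, medication adherence, physical activity, level of engagement, Self-Regulation of Eating Behavior") and five on quality of life and psychological state (quality of life, anxiety, depression, self-efficacy, social support).
- **Recruitment and sample size (2.2.1).** The trial is sized on SBP alone, with expected values of "138.2 mmHg for the routine health education group, 132.0 mmHg for the universal AI group, and 127.0 mmHg for the TCM-constitution–based AI group" and a common standard deviation that "is set at 16.3 mmHg". The calculation is a one-way ANOVA at alpha 0.05 with 90% power. It gives 55 per group, raised to 69 per group (207 in all) for 20% dropout.

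**The concern.** The analysis section and the sample-size section use different significance levels for the same test. The multiplicity sentence takes outcomes as its family and includes the primary. Bonferroni then divides 0.05 by the number of outcomes, and the primary has no protected share. The sample-size section makes no allowance for this. Its only warning about lost power concerns a true effect smaller than assumed.

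At stake is the conclusion on the trial's single primary outcome. If the multiplicity rule is applied as written, the trial is clearly smaller than its own 90% target requires. If SBP is instead tested at 0.05, the power statement holds but the published multiplicity rule has not been followed. Someone has to choose between these, and the text leaves room to choose after the results are known.

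**Working it through.** **Inputs.** From Recruitment and sample size: expected means 138.2, 132.0 and 127.0 mmHg; SD 16.3 mmHg; alpha 0.05; 55 evaluable per group (N = 165); 20% dropout. From Outcomes: 1 primary and 4 + 5 + 5 = 14 key secondary outcomes, with blood fat counted as one.

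**Step 1: reproduce the stated sample size.**
- Grand mean = (138.2 + 132.0 + 127.0)/3 = 132.4. Deviations are 5.8, −0.4 and −5.4.
- SD of the group means = √[(33.64 + 0.16 + 29.16)/3] = √20.99 = 4.58.
- Effect size f = 4.58/16.3 = 0.281.
- Noncentrality λ = N·f² = 165 × 0.0790 = 13.03, with 2 and 162 degrees of freedom.
- Power of the noncentral F test at alpha 0.05 is 90.3% with 55 per group and 89.8% with 54. So 55 is the smallest sufficient number.
- 55/(1 − 0.20) = 68.75, rounded up to 69 per group, 207 in all.

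The protocol's figures reproduce exactly.

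**Step 2: apply the plan's multiplicity rule.** The family is 1 + 14 = 15, so alpha = 0.05/15 = 0.00333. With the same f and 55 per group:

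| Outcomes in the family | Alpha for SBP | Power, 55 per group |
|---|---|---|
| 1 (as sized) | 0.05 | 90.3% |
| 10 | 0.0050 | 67.2% |
| 13 | 0.0038 | 64.1% |
| 15 (as listed) | 0.0033 | 62.4% |
| 17 (e.g. blood fat counted as three lipids) | 0.0029 | 60.9% |

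The loss at 15 outcomes is 90.3 − 62.4 = 27.9 percentage points, and it depends little on the exact count. If nobody dropped out (69 evaluable per group), power at 0.0033 would be 77.3%. Restoring 90% at 0.0033 takes 89 evaluable per group; 89/0.80 = 111.25, so 112 per group and 336 in all, against 207 planned.

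**Step 3: allow for the planned baseline adjustment.** The mixed model includes the baseline value, which reduces the residual SD roughly to 16.3·√(1 − r²), so λ becomes 13.03/(1 − r²). The documents give no r, so these values are assumptions:

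| Assumed r | λ | Power at 0.05 | Power at 0.0033 |
|---|---|---|---|
| 0.3 | 13.03/0.91 = 14.3 | 92.9% | 68.6% |
| 0.5 | 13.03/0.75 = 17.4 | 96.7% | 80.3% |
| 0.6 | 13.03/0.64 = 20.4 | 98.5% | 88.2% |
| 0.7 | 13.03/0.51 = 25.5 | 99.7% | 95.6% |

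With 55 per group, the single-family rule reaches 90% only if r is somewhat above 0.6.

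**The case against.** Several objections deserve an answer.

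**Bonferroni over all outcomes is valid.** It is conservative and does not inflate type I error, and preferring a hierarchy is partly a design choice. That stands. The fault is that the stated power belongs to a different significance level from the one the rule implies.

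**The planned analysis is stronger than the ANOVA.** This also stands in part, and Step 3 shows by how much. A reader might take 62% as a forecast for the mixed model. The documents do not support that: it is the figure on the protocol's unadjusted sizing model with exactly 55 evaluable per arm. Equally, the protocol states no baseline correlation that would justify claiming a recovery.

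**Bonferroni may be meant for the three pairwise contrasts within each outcome.** Tukey is only an example, so this is possible. But the sentence names outcomes as the family, and the pairwise step already has its own adjustment. The number of tests is never stated; 15 is a count from the outcome lists.

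**A full SAP may settle it.** The SAP may define the family in detail, and no omission is claimed here. The point is that two rules stated in the article do not fit together.

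**Stronger readings that the text does not bear out.**
- A reader might infer that the 0.05 threshold contradicts Bonferroni. It need not: if it refers to adjusted p-values the two sentences agree, and adjusted p < 0.05 is then the same as raw p < 0.0033. This is an ambiguity, not a proven contradiction.
- A reader might blame Bonferroni for weak power in the comparisons involving the universal AI group. Much of that weakness comes from sizing on an omnibus F test, which is a separate matter.
- A reader might see inflated error in the later sentence on combining p-values by Stouffer's method. That sentence is conditional, sits among the exploratory analyses and does not say which p-values would be combined, so no error rate can be attached to it.

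**Conclusion.** The point holds as a mismatch of significance level between sizing and analysis, and the plan is wrong as written in this respect. Taken literally, the primary SBP test is made at about 0.0033, while the trial is sized at 0.05. On the protocol's own model that means about 62% power instead of 90%. This rests on four assumptions: a family of 15 outcomes, the protocol's expected means and SD, 55 evaluable per arm, and no credit for baseline adjustment. The first matters little. The last matters more, since an assumed baseline correlation of 0.7 would lift power above 90%, but nothing in the document supports a particular value. The sample-size caveat about a smaller true effect does not cover this loss.

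**What to change.** In Statistical analysis:

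1. Take the primary out of the Bonferroni family. Test SBP at month 3 first, at the full two-sided 0.05.
2. Only if that test is significant, test the key secondary outcomes by Holm or Bonferroni within their own family at 0.05. Otherwise report them as estimates with confidence intervals.
3. State that the 0.05 threshold refers to multiplicity-adjusted p-values.

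This keeps family-wise control, brings the sizing and analysis levels into line, and restores the stated 90% on the protocol's sizing model. It takes a few sentences, adds no participants, and should be recorded before unblinding. The price is that key secondary outcomes can carry confirmatory claims only after the primary succeeds.

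If the sponsor prefers to keep one Bonferroni family, the sample-size section should state the number of outcomes in it and the power at the corrected level. Any credit for baseline adjustment should come with the correlation assumed and its justification. Keeping 90% power on the unadjusted model would instead need about 336 participants.
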